**Methods:**

The study is a multicentric randomized controlled trial, which will be conducted across 4 phases in Udupi, Mysuru, and Shivamogga districts of Karnataka. Phase 1 features a cross-sectional study design of 175 farmers to evaluate their baseline knowledge, attitudes, and practices on usage of pesticides. Phase 2 employs semi-structured interviews with 20–30 farmers and 10–20 key stakeholders, including pesticide dealers, scientists from Farm Science Centers [Krishi Vigyan Kendra (KVK)], and joint directors of agriculture to explore pesticide handling approaches, challenges, and community-specific needs while handling pesticides. The findings from Phases 1 and 2 will help in development and validation of an intervention in the form of educational video in Phase 3 which will be piloted. Phase 4 involves implementing the validated intervention and conducting long-term follow-up to assess the impact and sustainability. Phase 4 will be a two-arm, single-blind, parallel-group randomized controlled trial, with villages randomized 1:1 into intervention and control groups. The intervention group will receive a 15–20-minute educational documentary in the local language, while the control group will receive no intervention. The outcomes will be evaluated based on changes in Knowledge, Attitudes, and Practices (KAP) scores, with assessments conducted immediately post intervention, at 6 months, and at 12 months from the date of intervention. These will be correlated with outcomes including quality of life and laboratory parameters.

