### Trial design

This study adopts a multi-phase, mixed-methods approach to address pesticide safety practices among farmers in Karnataka state. The study will be conducted in 4 different phases. Phase 1 is an analytical cross-sectional study, designed to evaluate the baseline knowledge, attitudes, and practices (KAP) of farmers using structured questionnaires. Phase 2 involves qualitative face-to-face interviews to gain deeper insights into the behavioural and contextual factors influencing pesticide usage and safety practices.

Phase 3 involves development and validation of need-based education module, where selection of experts will be carried out by purposive sampling technique. Phase 4 is a multicentric RCT, where 3 districts that includes 6 villages will be selected based on randomization. This study will be conducted as a two-arm, single-blind, parallel group with simple randomization of the districts and cluster randomization of farmers. The allocation ratio is 1:1, with one arm receiving the educational intervention and the other serving as a control group with no intervention. The outcomes will be assessed in terms of mean difference with the pre and post assessment in terms of KAP. The trial adopts a superiority framework [33] to assess the effectiveness of the educational intervention in improving pesticide safety knowledge, attitudes, and practices among farmers.

The below Fig. 1 depicts the trial process from recruitment to randomisation.

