### Primary outcomes

The primary outcomes of the trial are (i) Knowledge, Attitude, and Practice (KAP) scores, assessed using a validated KAP questionnaire, and (ii) Quality of Life (QoL) scores, evaluated using the SF-36 Questionnaire. Both outcomes will be measured at baseline, post-intervention, and periodic follow-ups, with results analysed as mean changes over time and correlated with laboratory findings to provide a comprehensive understanding of the intervention’s impact.

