### Participant timeline

The trial will be conducted over a period of 3 years in 4 phases. During the phase 1, with duration of 8 months, 175 farmers will be recruited to assess their baseline knowledge, attitudes, and practices (KAP) regarding pesticide usage, which will be correlated with quality-of-life and biochemical parameters.

In the phase 2, which will last 4 months, around 20 to 30 farmers will participate in qualitative interviews to share their needs and perspectives on pesticide usage patterns, disposal methods, and storage practices. Additionally, 10 to 20 key stakeholders, including pesticide dealers, scientists from Farm Science Centre [Krishi Vigyan Kendra’s (KVK’s)], joint directors of agriculture, assistant director of agriculture, subject matter specialist [SMS] will be involved from the selected villages across different districts, to gather qualitative insights and recommendations regarding pesticide usage patterns.

Following this, phase 3 will be conducted over 6 months, which focuses on the development and validation of the educational module. This phase will be followed by a pilot implementation lasting further 6 months.

The final phase 4 will be executed as a randomized controlled trial (RCT), where the validated educational module will be implemented in the selected villages for a specific duration of 2 months. Participants will be followed up at intervals of 6 months and 12 months. The total duration of phase 4 will be 1 year.

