## Methods: data collection, management, and analysis

### Data collection and management

In phase 1, data will be collected in person through face-to-face interactions using baseline questionnaires, including the KAP questionnaire and the SF-36 Quality of Life (QoL) questionnaire from RAND Health. Additionally, qualitative interviews will be conducted, and laboratory tests (blood samples) will be collected from enrolled participants. All quantitative data will be stored in OpenEpi version 3.1 software and later transferred to SPSS version 20.0 (IBM, New York, NY, USA) for statistical analysis.

In phase 2, qualitative interviews will be recorded with prior consent, transcribed, and stored securely on a password-protected device. These recordings will be transcribed and translated to verbatim, and themes and sub-themes will be developed using NVivo software for qualitative analysis.

In phase 3, after developing the educational documentary, its validation will be conducted using a Likert scale (ranging from 1 to 4) and face-to-face focus group discussions (FGDs). These discussions will be recorded, transcribed, translated, and analysed to extract themes and suggestions, which will be incorporated to refine the documentary.

In phase 4, pre- and post-intervention questionnaires will be administered to both the intervention and control groups, mirroring the data collection process from Phase 1. The collected data will be stored in OpenEpi version 3.1 software and subsequently analysed using SPSS version 20.0 (IBM, New York, NY, USA).

Throughout the study, participant identities will remain anonymized, and all data will be coded for confidentiality. At the conclusion of the study, data will be discarded as per study protocols. Missing data, such as those resulting from loss to follow-up or participant withdrawal, will be documented with appropriate justifications and reported in the results.

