### Statistical analysis

All data collected through the KAP and QoL questionnaires will be entered into SPSS version 20.0 (IBM, New York, NY, USA) for statistical analysis. Paired t-tests will be performed for continuous variables to compare pre- and post-intervention results. For improvements in quality of life and changes in laboratory parameters, the Wilcoxon Signed Ranks Test will be used. The results from the KAP surveys will be presented as mean ± standard deviation (SD). Qualitative interview data will be analysed using NVivo software, with thematic analysis to identify key patterns, insights and to understand the needs and perception of the farmers. Subgroup analyses based on confounding factors such as age, gender, and education level will be conducted to assess differential effects of the intervention. An intention-to-treat analysis will be performed and per-protocol analysis for participants deviating from the protocol.

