## Conclusion

The study aims to educate farmers through a need-based approach, where data will be collected directly from farmers to identify specific inducer needs. This initiative is designed not only to enhance their knowledge but also to improve their practices in minimizing hazards associated with pesticide usage. A key focus of the study design is to assess knowledge retention and behavioural changes over time, ensuring the long-term sustainability. To our best knowledge, this is the first study from South India region to evaluate the implementation of a need-based educational intervention using a mixed-method approach within an RCT design.

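### Retention to 12 months is a key focus and follow-up readings are planned, but the named tests are pre/post comparisons with 'post' undefined, and none compares the arms or estimates how much of the gain is kept

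*Protocol article*

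**What the plan says.** **Aim and schedule.** The Conclusion states: "A key focus of the study design is to assess knowledge retention and behavioural changes over time, ensuring the long-term sustainability". The Methods part of the Abstract schedules Phase 4 outcomes "with assessments conducted immediately post intervention, at 6 months, and at 12 months from the date of intervention". Participant timeline repeats the later visits: "Participants will be followed up at intervals of 6 months and 12 months". Primary outcomes covers KAP and SF-36 scores together: "Both outcomes will be measured at baseline, post-intervention, and periodic follow-ups, with results analysed as mean changes over time".

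**Method.** Trial design puts the outcome in two-occasion form: "The outcomes will be assessed in terms of mean difference with the pre and post assessment in terms of KAP". Data collection and management says: "In phase 4, pre- and post-intervention questionnaires will be administered to both the intervention and control groups", and does not name the 6- and 12-month visits there. Sample size bases Phase 4 on a paired t-test formula and gives neither an expected difference nor a resulting number of farmers. Statistical analysis then names the tests: "Paired t-tests will be performed for continuous variables to compare pre- and post-intervention results", and "For improvements in quality of life and changes in laboratory parameters, the Wilcoxon Signed Ranks Test will be used". Trial design also describes two arms allocated 1:1, a superiority framework, and six villages in three districts.

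**The concern.** Retention is a contrast between visits: how much of the effect seen straight after the documentary is still there a year later. In a two-arm trial it is a contrast of arm differences. A paired pre/post test answers another question, namely whether the same people's scores moved between two occasions.

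The article justifies the trial by the short follow-up of earlier studies, so its distinctive contribution would be the long-term result. If the named tests are applied as written, that result either goes untested or is judged by a test against baseline, which a largely faded gain can still pass. Since the tests are within-person, a change shared by the control arm would also not be separated from the effect of the documentary.

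**Working it through.** The plan states no figure on this point, so there is nothing to reproduce. The check has two parts: what the named tests can estimate, and an illustration.

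**1. The two readings of 'post'.** Write the mean reading in an arm as B (baseline), I (immediate), M6 and M12.

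- If 'post' is the immediate visit, the test is of I − B. No named test uses M6 or M12.
- If 'post' is every visit, the tests are of I − B, M6 − B and M12 − B, separately in each arm. None is a test or interval for M12 − I, and none sets one arm against the other.
- The signed-rank test for quality of life has the same two-occasion structure.
- Primary outcomes speaks of mean changes over time but names no reference visit, contrast, arm comparison or method.

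**2. Illustration: can a faded gain pass a test against baseline?**

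Inputs:
- SD 10.33, from Sample size. It is the SD of a baseline score. Used as the SD of change, it assumes a within-person correlation of 0.5, since 10.33 × √(2 × (1 − 0.5)) = 10.33.
- 79 farmers per arm, an assumption borrowed from Phase 1: 175 × 0.9 / 2 = 78.75. The lower value, 30 per arm, is also an assumption. Phase 4 gives no number.
- Immediate gain 8 points, falling to 3 at 12 months (5/8 = 62% lost) or to 4 (half lost). Assumed.
- Two-sided 5%. Village clustering ignored.

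Formula: SE = 10.33/√n; noncentrality = 12-month change / SE; power from the noncentral t on n − 1 degrees of freedom.

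| Per arm | SE | 12-month change | Noncentrality | Probability significant against baseline |
|---|---|---|---|---|
| 30 | 1.886 | 3 | 1.59 | 0.34 |
| 79 | 1.162 | 3 | 2.58 | 0.72 |
| 30 | 1.886 | 4 | 2.12 | 0.54 |
| 79 | 1.162 | 4 | 3.44 | 0.92 |

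The result also moves with the correlation. For the fall to 3 points, correlations of 0.3 and 0.7 (SD of change 12.22 and 8.00) give 0.26 and 0.51 at 30 per arm, and 0.58 and 0.91 at 79.

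**3. Would a between-arm test at 12 months be enough?** It supplies the missing arm comparison, but not the amount kept. Assume no change in controls, SD 10.33 and 79 per arm. The SE is 10.33 × √(2/79) = 1.644, so a 3-point arm difference has noncentrality 3/1.644 = 1.83 and is significant with probability 0.44. A 4-point difference has noncentrality 2.43 and probability 0.68. A significant 12-month arm difference therefore shows that an effect is still present. It does not show that the immediate effect was retained.

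**The case against.** The strongest reply is that Primary outcomes plans measurement at periodic follow-ups and analysis over time. That stands against two stronger readings:

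- A reader might infer that Phase 4 collects only two readings. It does not: the Abstract, Primary outcomes and Participant timeline all plan later ones. Trial design and the data-collection wording can be read as shorthand.
- A reader might infer that no over-time analysis is planned at all. That is too absolute. An over-time summary is stated, and means with SDs reported by visit would make a fall from 8 points to 3 visible. What is missing is a contrast, an arm comparison and an interval.

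It may also be said that model details belong in an analysis plan that is not shown. True of covariance structures and missing-data methods. But the article does commit to specific tests, and those do not fit its stated focus. Nor does it help that the listed objective asks only for impact on KAP and quality of life: the Abstract says Phase 4 assesses sustainability. An effect still present at 12 months is a fair reading of that word, but it too needs an arm comparison.

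Two further inferences are not supported. One is that the trial will tend to overstate sustainability; it could, depending on numbers that Phase 4 does not give. The other is that dropout must seriously inflate apparent retention. In a simulation with assumed selective dropout (log-odds slope 1 per SD of early gain, correlation of gains 0.6, a 4.6-point gain halving), true retention of 50% appeared as 62% at 10% dropout and 73% at 20%. That was when 12-month attenders were set against everyone's immediate reading. Using the same farmers at both visits gave 52% and 53%.

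**Conclusion.** The point holds as a mismatch between a stated aim and the stated tests. Follow-up readings are planned and retention is a key focus, yet every named test of the trial outcomes compares two occasions within person, leaves 'post' undefined, and neither compares the arms nor estimates the change from the immediate to the 12-month reading. This does not depend on any numerical assumption: rejecting no change from baseline says nothing about the share of the gain that is kept.

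The size is illustrative only. With an 8-point gain falling to 3 and an SD of change of 10.33, the chance of a significant 12-month result against baseline is about 0.34 at 30 per arm and 0.72 at 79. The sample sizes, the gain and the use of 10.33 as an SD of change are all assumptions. The plan should be changed, but the fault lies in the analysis wording and not in the visit schedule.

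**What to change.** Reconcile Trial design, Primary outcomes, Data collection and management, and Statistical analysis:

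1. List the four Phase 4 readings (baseline, immediate, 6 months, 12 months) in both arms.
2. For the trial comparison, replace the paired pre/post tests with one longitudinal model with arm-by-visit terms, using all available readings and allowing for village clustering with a small-sample correction, since there are only six villages.
3. Prespecify the 12-month arm difference as the test of lasting effect.
4. Report separately the change in arm difference from the immediate to the 12-month reading, with its 95% CI, as the estimate of retention.
5. Fix the wording of claims. A 12-month arm difference whose CI excludes zero is an effect still present at 12 months. Statements on how much was retained rest on the change estimate and its interval.

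**Cost.** Changes to analysis wording and one model; no new visits or data. The clustering correction needs care with six villages, intervals will be wide, and some sustainability claims will be weaker.

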### Sample size

The sample size for each phase of the study was calculated distinctly, tailored to the study design and objectives. A formal power calculation was conducted to ensure appropriate statistical power for detecting meaningful differences.

For phase 1, the sample size was determined using data from Sam KG et al. (2007) [31], a study conducted in Udupi, Karnataka, India, which reported a baseline Knowledge, Attitude, and Practice (KAP) score of 30.88 with a standard deviation of 10.33. The required sample size was calculated using the following formula for comparing two means:

$$\mathrm{n}\;= \;2\times\;[(\mathrm{Z}_{\alpha/2}\;+\;\mathrm{Z}_{\beta})\;/\;\mathrm{Z}_{\delta}\;]^{2}$$ where, n = required sample size per group, Z_α/2_
**=** standard normal deviate for a given significance level (e.g., 1.96 for 5% significance level), Z_β_ = standard normal deviate for the desired power (e.g., 0.84 for 80% power), σ = standard deviation of the outcome variable (10.33 from prior study) and Z_δ_ = expected mean difference in the effect size.

A statistical power of 80% was chosen, which is widely considered an acceptable standard in health and social science research [40]. A power of 80% indicates that there is an 80% probability of detecting a true effect if one exists, while maintaining a Type I error (α) of 5%. Accounting for a 10% dropout rate, a total of 175 farmers will be selected using the stratified sampling method for the KAP assessment, quality of life evaluation, and laboratory investigations.

In phase 2, with approximately 20-30 farmers and 10–20 stakeholders from various villages across the selected 3 districts will be involved in the qualitative interviews for the need assessment phase.

Phase 3 focuses on the development and validation of the educational intervention by 6 experts from various domains including experts from agricultural sciences, pharmacy practice, community medicine, public health, and emergency medicine.

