For Phase 4, the sample size was determined based on findings from a pilot study involving 12 farmers, with equal allocation to intervention and control groups in a simple randomized controlled trial (RCT) design. The final sample size was calculated using the power calculation formula for a paired t-test:$$\mathrm{n}\;=\;2\times\;[(\mathrm{Z}_{\alpha/2}\;+\;\mathrm{Z}_{\beta})^{2}\;*\;2\sigma^{2}\;/\;\mathrm{Z}_{\delta}\:^{2}]$$, where, n = required sample size per group, Z_α/2_**=** standard normal deviate for a given significance level (e.g., 1.96 for 5% significance level), Z_β_ = standard normal deviate for the desired power (e.g., 0.84 for 80% power), σ = standard deviation of the outcome variable (10.33 from prior study) and Z_δ_ = expected mean difference in the effect size.

To ensure the effective implementation of the educational intervention, farmers will be stratified by age and education level.

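### The plan promises subgroup analyses of differential effect, but the only tests it names are within-person pre/post tests, which cannot test a difference in effect between subgroups

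*Protocol article*

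**What the plan says.** The Statistical analysis section of the protocol article sets the subgroup aim in one sentence: "Subgroup analyses based on confounding factors such as age, gender, and education level will be conducted to assess differential effects of the intervention". No test or model is attached to it.

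The same section names two tests for the quantitative outcomes. For continuous variables: "Paired t-tests will be performed for continuous variables to compare pre- and post-intervention results". For the other outcomes: "For improvements in quality of life and changes in laboratory parameters, the Wilcoxon Signed Ranks Test will be used". Both work on each farmer's own before/after difference.

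Other sections point the same way. Under Sample size, Phase 4 is sized as follows: "The final sample size was calculated using the power calculation formula for a paired t-test". Under Primary outcomes, KAP and SF-36 results are to be analysed as mean changes over time. The article nowhere names an interaction term, a between-arm test or a regression model.

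**The concern.** A differential effect is a difference between effects: film minus control in one subgroup, compared with film minus control in another. Its null hypothesis is that the two effects are equal. A paired test within a subgroup has another null, that scores in this subgroup did not change. Its p-value depends on the size of the subgroup as well as on the gain, so a small subgroup can miss significance with the same true gain as a large one. It also leaves out the control arm, so the change it tests is not an intervention effect.

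What is at stake is the claim about who benefits from the film. The Background names low literacy as a reason why earlier education programmes fell short, and education level is one of the three listed factors. A finding that the film works in more educated but not in less educated farmers could steer later programmes, and it might reflect only subgroup size.

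The point is distinct from the choice of test for the overall effect. Even with a between-arm main analysis, separate p-values per subgroup would still not test whether effects differ.

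**Working it through.** **The plan's own figures.** The article states no Phase 4 sample size, subgroup size or subgroup error rate, so there is nothing to reproduce directly. The only N from a power calculation is 175, for Phase 1. The mean difference behind it is described as "expected mean difference in the effect size" and has no number, so 175 can only be back-solved. With SD 10.33, 5% two-sided and 80% power, a difference of 4.6 points gives 2 × [(1.96 + 0.84) × 10.33 / 4.6]² ≈ 79.1, so 80 per group and 160 in total. With 10% dropout that is 178 (160/0.9) or 176 (160 × 1.1). This is consistent with 175 but does not reproduce it.

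**Inputs.** From the article: 5% two-sided, 80% power, SD 10.33, 1:1 allocation. Assumed: 30, 60 or 88 farmers in the film arm; the true gain in SDs of change; the subgroup split. Clustering is ignored.

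**Step 1: identical true effects.** If two disjoint subgroups have powers p₁ and p₂ for the paired test, the chance that exactly one is significant is p₁(1 − p₂) + p₂(1 − p₁). With no true change this is 2 × 0.05 × 0.95 = 9.5%. With a common true gain (powers from the noncentral t distribution):

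| True gain | n in film arm | 50:50 split | 20:80 split |
|---|---|---|---|
| 0.3 SD | 30 | 31% | 33% |
| 0.3 SD | 60 | 46% | 52% |
| 0.3 SD | 88 | 50% | 61% |
| 0.8 SD | 88 | 0.1% | 11% |

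Example, 0.3 SD, n = 88, split 18 and 70: powers 0.225 and 0.697, so 0.225 × 0.303 + 0.697 × 0.775 = 0.61.

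**Step 2: tie the power to the plan.** If the paired test has 80% power overall, its noncentrality is 1.96 + 0.84 = 2.80.
- Equal halves: 2.80 × √0.5 = 1.98 each, power 51%, discordance 2 × 0.508 × 0.492 = 50%.
- 80:20 split: 2.80 × √0.8 = 2.50 (power 71%) and 2.80 × √0.2 = 1.25 (power 24%), discordance 0.707 × 0.760 + 0.240 × 0.293 = 61%.

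The printed Phase 4 formula, read as n per group, is 4σ²(1.96 + 0.84)²/δ². With pre/post correlation ρ, the SD of change is σ√(2(1 − ρ)), so the paired noncentrality is 2 × 2.80 / √(2(1 − ρ)).
- ρ = 0.5: noncentrality 5.60; discordance 4% for halves and 29% for 80:20.
- ρ = 0: 32% and 57%.
- ρ = 0.7: 0.2% and 10%.

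**Step 3: the test that matches the question.** In simulations with identical effects (20,000 per setting), an arm-by-subgroup interaction test on change scores was significant in 4.7% to 5.3% of trials. Over three independent factors the chance of at least one false positive is 1 − 0.95³ = 14%.

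**Step 4: power of that test.** Suppose true film-arm gains of 0.5 and 1.0 SD, halves, and a control arm of equal size with no change. The interaction is a contrast of four cell means, each with n/2 farmers, so its SE is √(4/(n/2)).
- n = 60 per arm: SE = √(4/30) = 0.365; 0.5/0.365 = 1.37; power about 28%.
- n = 88 per arm: SE = √(4/44) = 0.302; 0.5/0.302 = 1.66; power about 38%.

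Discordant paired tests would flag the same doubling in about 25% (n = 60) and 10% (n = 88) of trials. At n = 88 both subgroups are usually significant.

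**The case against.** The strongest objection is that the article does not say that paired tests will be run in each subgroup, nor that a mix of significant and non-significant results will be read as a difference. The subgroup model is also a detail that an article may leave to an analysis plan, and the stated aim is compatible with an interaction test. The first part stands: the per-subgroup paired test is an inference. The second stands only in part. The article does not merely stay silent. It commits to an aim and to a set of tests, and no test in that set can serve the aim.

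Three stronger readings are tempting, and the documents do not support them.

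- A reader might infer that false subgroup differences will be reported often. The unstated inputs decide this: with large gains and balanced subgroups the rate is close to zero. At 0.3 SD, only n = 88 (79% overall paired power) is near the planned 80%; n = 30 and n = 60 give 36% and 63%.
- A reader might infer that the fix greatly improves detection of real differences. Comparing gains between subgroups inside the film arm alone would have about 48% (n = 60) and 64% (n = 88) power for the doubling. That comparison ignores the control arm and is not the interaction proposed here, which has 28% and 38%.
- A reader might infer, because the sentence labels the variables as confounders, that subgrouping is meant to remove confounding. The same sentence gives its purpose as differential effects, and the randomization section uses these variables in allocation. The label is a slip of terminology.

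**Conclusion.** The point holds in a limited form. The Statistical analysis section states a question about differential effects and names only tests of within-subgroup change. Carried out as written, the plan cannot answer that question, and comparing subgroup p-values could mislead.

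How often it would mislead cannot be fixed from the article. Per factor it is about 30% to 60% when subgroup power is moderate (0.3 SD gain, 30 to 88 in the film arm) and about 0% to 11% at 0.8 SD with 88. An interaction test gives about 5% per factor, or 14% over three independent factors. These figures rest on assumed sizes, gains and splits, on normal changes, and on no clustering by village.

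The benefit of the change is control of false claims, not power. Subgroup effects are neither primary nor secondary outcomes, so this is a modest correction that is worth making because it costs so little.

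**What to change.** Replace the subgroup sentence in the Statistical analysis section with: *Differential effects by age, gender and education will be explored by the arm-by-subgroup interaction in a between-arm model for KAP and QoL that allows for village, reported as the difference in effect with 95% CI; within-subgroup p-values will not be used to claim a difference.* Drop the description of these variables as confounders.

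The cost is one sentence and three interaction terms per outcome, on data already to be collected. The downside is fewer subgroup claims and wide intervals. With six villages the intervals may be wider than the figures above suggest, if the subgroup difference varies between villages.

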### Intervention

The primary component of the intervention will be a 15–20-minutes educational documentary in the local language. Topics like safe pesticide usage, proper storage, disposal methods, and associated health risks will be covered in this documentary. These elements will be presented through a story that will be displayed as a short documentary or movie among the farmers. Cluster sampling method will be utilised for selecting participants based on characteristics including age, education, and years of experience with pesticides or agriculture. The intervention will be provided in the intended villages at community centres or village halls.

The control group will not receive any educational intervention during the study period. Participation records will be maintained to track adherence to intervention, and any participant’s decision to withdraw from the study will be documented. If withdrawn, data collected up to the point of withdrawal will be retained for analysis. The appropriate reason will be documented for withdrawal if available.

To maintain the integrity of the study, participants will be requested to refrain from engaging in other pesticide-related educational initiatives, although they may continue their regular farming activities. Adherence to the intervention and pesticide practices will be monitored through regular follow-up calls, personal visits, and collaboration with field officers, community leaders, and local organizations.

The detailed participant timeline has been provided in Fig. 2, following the SPIRIT 2025 format [39] .

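### The per-protocol analysis is assigned to the farmers who deviate, and the paired tests named do not by themselves deliver the promised intention-to-treat analysis

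*Protocol article*

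**What the plan says.** The protocol article deals with analysis populations in one sentence, at the end of Statistical analysis: "An intention-to-treat analysis will be performed and per-protocol analysis for participants deviating from the protocol". Neither set is defined anywhere else in it.

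The same section names the tests. For continuous variables: "Paired t-tests will be performed for continuous variables to compare pre- and post-intervention results". For quality of life and laboratory parameters, "the Wilcoxon Signed Ranks Test will be used".

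Two other statements bear on who is analysed. Under Data collection and management: "Missing data, such as those resulting from loss to follow-up or participant withdrawal, will be documented with appropriate justifications and reported in the results". Under Intervention: "If withdrawn, data collected up to the point of withdrawal will be retained for analysis". The Intervention section also plans the information needed to identify adherence: "Participation records will be maintained to track adherence to intervention".

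Trial design describes Phase 4 as a two-arm superiority trial. The Abstract places assessments immediately after the intervention, at 6 months and at 12 months.

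**The concern.** **Per-protocol set.** The term has a settled meaning: participants without important departures from the protocol. The sentence attaches it to the opposite group. Followed literally, the result labelled per-protocol would describe, for example, intervention farmers who missed the screening and control farmers who saw the film. It would say nothing about the effect in those who received the programme as intended.

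Deviations are to be expected. The film is shown at a village hall or community centre, participants are only asked to stay away from other pesticide education, and the Discussion itself notes that farmers have little time for meetings. Under Blinding, outcome assessors and data analysts know the allocation. A set whose membership is unclear could therefore be settled by people who have already seen results by arm.

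**Intention-to-treat set.** The promise covers all randomised farmers. A paired test needs two values per farmer, so on observed data it covers only those with both. The intention-to-treat label could then be attached to what is in fact a complete-pair analysis at each visit.

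**Working it through.** No figure in the article needs to be reproduced for this point; the check is of the text.

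**Step 1: the per-protocol sentence.** Let R be all randomised farmers and D those with a deviation.

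- Usual per-protocol set: R without D.
- Set as the sentence reads: D.
- Overlap: none, because the two sets are complements within R.

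A search of the other sections that touch on adherence or withdrawal (Intervention, Data collection and management) finds no definition that reverses this.

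**Step 2: who enters a paired test on observed data.** The visits are baseline, immediately post-intervention, 6 months and 12 months.

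| Last assessment completed | Immediate pair | 6-month pair | 12-month pair |
|---|---|---|---|
| Baseline only | no | no | no |
| Immediate post | yes | no | no |
| 6 months | yes | yes | no |
| 12 months | yes | yes | yes |

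A farmer who withdraws part-way still contributes a pair at each visit already completed. The commitment that "data collected up to the point of withdrawal will be retained for analysis" can therefore be met in part by paired tests. What they omit is every farmer lacking the relevant later value, and at all visits the farmer with a baseline value only.

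**Step 3: set this beside the missing-data statement.** Missing values "will be documented with appropriate justifications and reported in the results". That is a reporting rule. It neither excludes such farmers nor says how they stay in. The step from paired tests to a complete-pair analysis is thus an inference that holds if the tests are run on observed data.

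**Step 4: size.** If a fraction d of randomised farmers lacks the value at a visit, a fraction d is absent from that visit's paired test. The article gives no d and no N for Phase 4. For scale only, with d assumed between 5% and 20%, the number absent per 100 randomised farmers is 100 × 0.05 = 5 to 100 × 0.20 = 20.

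**The case against.** **The per-protocol wording may be loose drafting.** The authors may have meant a per-protocol analysis to deal with deviators. That is plausible. Even so, the sentence does not say whether deviators are left out, analysed separately or moved to another arm, and on its plain reading it is wrong. An analysis plan that defined the set properly would disagree with the published protocol. The objection reduces the likely harm but does not remove the error.

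**The intention-to-treat promise is not contradicted.** This stands. A reader might infer that the paired tests drop everyone without follow-up and so refute the promise. The article never says such farmers are excluded. Paired tests can be run on imputed data, and the handling of missing values may properly sit in an analysis plan that is not at hand. The absence of a method is not a finding here.

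**Partial data can be used.** A reader might also infer that withdrawn farmers' data cannot enter a paired test at all. The visit schedule shows otherwise: leaving after the immediate or the 6-month assessment still yields a pair at each completed visit.

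**The size cannot be taken from Phase 1.** It is tempting to apply the 10% dropout to the 175 farmers under Sample size. Both figures belong to the cross-sectional Phase 1, not to the randomised trial, so they describe no planned intention-to-treat or per-protocol analysis.

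**The direction of bias is not documented.** That a complete-pair analysis would favour one arm is conjecture. The article gives no dropout by arm, and the named tests are within-farmer comparisons.

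**Conclusion.** The per-protocol sentence is an error of statement and should be corrected. It names the complement of the intended population, and no other part of the article repairs it. This conclusion rests on the text alone and on no assumed number.

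The intention-to-treat part holds only as a tension: run on observed data, the named tests use farmers with both values, so by themselves they do not deliver an analysis of all randomised farmers. It rests on the assumption that no imputation is applied, which the article neither states nor rules out. It cannot be quantified, because the article states neither a sample size nor a dropout rate for Phase 4.

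The matter is not fatal to the trial. It warrants correction before data are analysed, because the analysts are unblinded.

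**What to change.** Replace the sentence on analysis sets with wording such as:

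> Primary (intention-to-treat): all enrolled farmers, analysed in the arm to which their cluster was randomised, whether or not they attended the screening. All available assessments enter a repeated-measures mixed model with arm, visit, arm-by-visit interaction and a cluster (village) effect. Sensitivity (per-protocol): as above, excluding farmers with prespecified major deviations, for example non-attendance at the screening in the intervention arm or exposure to the film in the control arm, identified from the participation records.

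Three points on use:

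- Treat baseline as one of the visits in the model, so that a farmer with baseline only is retained. The model's validity then rests on missing values being explained by the observed data, and this should be stated.
- The cluster effect must match the unit actually randomised. Recruitment of participants says districts are allocated, whereas Random sequence generation and randomization says villages are. The wording above assumes villages, and the two sections need to be reconciled first.
- Trial design mentions six villages. If that is the total, a two-arm comparison leaves 6 − 2 = 4 degrees of freedom between villages, so a small-sample correction should be specified.

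The cost is a somewhat longer model specification in place of the two paired tests. No extra assessments are needed: participation records are already planned, and exposure in the control arm can be noted during the follow-up calls and visits that the Intervention section already foresees. The minimum change, if the tests are left for the analysis plan to settle, is the one clause that defines per-protocol as farmers without major deviations.
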